### Secondary outcome measures

All participants will be assessed at baseline and at six months by an assessor blinded to group allocation. The secondary outcome measures include:

(i) *Foot pain*: the Manchester Foot Pain and Disability Index (MFPDI) will be used to assess foot pain [39]. The MFPDI consists of 19 statements prefaced by the phrase "Because of pain in my feet", formalised under three constructs: functional limitation (10 items), pain intensity (five items), and personal appearance (two items), with three possible answers: "none of the time" (score = 0), "some days" (score = 1), and "most days/every day" (score = 2). The last two items are concerned with difficulties in performing work or leisure activities, which are omitted if the respondent is of retirement age. The total score (range: 0 to 34) will be used to measure the degree of improvement in foot pain. The MFPDI has been shown to be a suitable tool for assessing foot pain in the older population [44], has high construct validity and has been shown to be sensitive to improvement following a self-management intervention [45].

(ii) *Physiological falls risk*: changes in physiological falls risk will be assessed using the Physiological Profile Assessment (PPA) [5]. Based on the performance of five physiological domains (vision, proprioception, strength, reaction time and balance), the PPA computes a falls risk score (standardised score) for each individual; this measure has a 75% predictive accuracy for falls in older people [46]. The five assessment items (Figure 5) are a test of vision (edge contrast sensitivity using the Melbourne Edge test), peripheral sensation (lower limb proprioception), lower limb strength (knee extension strength), reaction time using a finger press as the response, and body sway (sway when standing on a medium density foam rubber mat). Details regarding each of these tests are provided elsewhere [5]. Several studies have reported significant improvements in PPA scores following exercise interventions [47,48].

**Figure 5 F5:**
[figure not shown]
**The short-form Physiological Profile Assessment tests. **A: Visual contrast sensitivity, B: proprioception, C: knee extension strength, D: reaction time, E: postural sway standing on a foam rubber mat.

(iii) *Fear of falling*: Fear of falling will be measured using the 7-item short Falls Efficacy Scale-International (FES-I) [49]. The FES-I uses a Likert scale to score the participant's level of concern regarding the possibility of falling when performing certain activities of daily living (e.g. taking a bath/shower or climbing up or down stairs). There are four responses which are: "not at all concerned" (score = 1), "somewhat concerned" (score = 2), "fairly concerned" (score = 3) and "very concerned" (score = 4). The total score ranges from 7 (no concern about falling) to 28 (severe concern about falling). The FES-I has been shown to have excellent validity [50] and reliability in the older people (Cronbach's alpha 0.92, ICC = 0.83) [49].

(iv) *Generic health related quality of life*: Mental and physical health status will be measured with the Mental (MCS-12) and Physical (PCS-12) Component Summary scores of the short form Health Survey (SF-12). The SF-12 was developed and validated as a shorter alternative to the SF-36 [51]. To calculate PCS-12 and MCS-12 scores, SF-12 items are scored and normalized via a standardised algorithm. PCS-12 and MCS-12 scores range from 0 to 100, with higher scores indicating better functioning. The MCS-12 and PCS-12 were designed to have a mean score of 50 and a standard deviation of 10 in a representative sample of the US population [52]. Test-retest correlations of 0.89 and 0.76 were observed for the 12-item PCS-12 and the MCS-12, respectively [51].

(v) *Foot and ankle strength*: Maximal isometric muscle strength of foot and ankle muscles (ankle dorsiflexion, plantarflexion, inversion and eversion, hallux plantarflexion and lesser toe plantarflexion) will be assessed as the average of three trials using a hand held dynamometer (Citec, CIT Technics, Haren, The Netherlands). Using hand-held dynamometry for testing foot and ankle strength has been shown to have good reliability (ICC 0.88 to 0.95) [53]. Plantarflexion strength of the toes will also be tested using the paper grip test, where the participant is seated with their knee and ankle at 90°, and instructed to use their toe muscles to push down on a 1 mm piece of card (e.g. a business card) while the examiner stabilises their ankle and attempts to slide the card away from the toes (Figure 6A). An inability to hold the card on any one of three trials is recorded as a fail. Using receiver operating characteristics (ROC) curves, this test has been shown to have a positive predictive value of detecting weakness of 95% for the hallux and 90% for the lesser toes [54]. Maximal isometric muscle strength for ankle dorsiflexion will also be measured as the maximum of three trials with the participant sitting in a high chair with their foot secured to a footplate attached to a spring gauge (Figure 6B). This test has been shown to have good reliability (ICC 0.88) [5]. Testing will be conducted on the self-reported dominant side identified by the response to the question "Which foot would you use to kick a ball with?".

**Figure 6 F6:**
[figure not shown]
Muscle strength assessment of A: toe plantarflexors, and B: ankle dorsiflexors.

(vi) *Foot and ankle range of motion*: First metatarsophalangeal joint dorsiflexion range of motion will be measured using a goniometer as the maximum angle at which the hallux cannot be passively moved into further extension in a non-weightbearing position (Figure 7A). The reliability of this test (ICC 0.95) has been reported previously [55]. Ankle dorsiflexion flexibility will be recorded using a modified version of the lunge test which has been shown to have high reliability (ICC = 0.88) [56]. Participants will be asked to take a comfortable step forward and squat as low as possible, keeping their trunk upright, without lifting the heel of their backfoot from the ground. The degree of motion will be recorded using a digital inclinometer placed on the mid-point of the anterior tibial border (Figure 7B). The test will be conducted with the knee extended and then with the knee flexed [57,58]. To assess ankle inversion and eversion, participants will be seated with the lower leg unsupported. Landmarks will be made on the participants at the midpoint between the malleoli on the anterior aspect of the ankle, the midline on the anterior aspect of the lower leg using the crest of the tibia as a reference point, and the longitudinal midline on the anterior surface of the second metatarsal. A flexible universal goniometer will be aligned along the landmarks and the participants will move their ankle from a self-selected neutral position actively to the end of range of inversion and eversion (Figure 7C). High intra-observer reliability has been reported for these tests (ICC 0.82 to 0.96) [59]. Testing will be conducted on the self-reported dominant side.

**Figure 7 F7:**
[figure not shown]
**Assessment of joint range of motion in the foot. **A: first metatarsophalangeal joint, B: ankle joint dorsiflexion, C: ankle joint complex inversion/eversion.

(vii) *Balance and functional ability*: Balance will be assessed through four tests. Postural sway will be measured as previously described in the section regarding the PPA (Figure 8A). The reliability (ICC 0.57 to 0.68) of this test has been reported previously [60]. Lateral stability will be measured using a sway meter that measures displacement of the body at the waist with testing performed with the participant standing with one foot in front of the other. Participants will choose which foot to place in the forward position and will be instructed to stand as still as possible for 30 seconds. Lateral displacement of the body will then be recorded [61]. Leaning balance will be measured using the maximum balance range test and coordinated stability tests [62]. For the maximum balance test, (Figure 8B) the sway meter is attached around the waist with the rod extending anteriorly. Participants are asked to lean forward then backwards from the ankles without moving their feet, as far as possible, i.e. to the point where they can just retain their balance. Maximal anterior-posterior displacement is measured over three trials. Using similar apparatus, the coordinated stability test (Figure 8C) requires the participant to bend and rotate at the hips without moving their feet to move the sway meter pen around a convoluted track marked on a piece of paper attached to the top of an adjustable height table. A total error score is calculated by summing the number of occasions the pen strays outside the track [62]. Good reliability has been reported for both the maximum balance test (ICC = 0.74) and the coordinated stability test (ICC = 0.83) [62] and both tests are predictive of falls[63]. These tests will be performed twice, once with the participant barefoot and again with their preferred outdoor footwear. Lateral stability, maximum balance range, coordinated stability and walking speed will be corrected for height prior to analysis [11].

**Figure 8 F8:**
[figure not shown]
**Balance and functional tests.** A = postural sway, B = maximal balance range, C = coordinated stability, D = sit to stand, E = alternate step test, F = walking speed.

Functional ability will be evaluated using the sit to stand test (time taken to rise from a 43 cm high chair five times without using the arms) (Figure 8D), alternate stepping test (the time taken to alternately place each foot on a 19 cm high step eight times) (Figure 8E), and walking speed over 6 metres (Figure 8F). These tests have been shown to be reliable in previous studies of older people (sit to stand (ICC = 0.89) [64], alternate stepping test (reliability coefficient of 0.98) [65] and 6 m walk (reliability coefficient of 0.93) [66] and have demonstrated good sensitivity and specificity in identifying multiple fallers [38].

### Sample size

The sample size for the study has been determined *a priori *using an appropriate sample size formula [67]. A sample size of 143 participants in each group provides 80% power to detect a 30% reduction in the intervention group in the primary outcome of the percentage of fallers. This reduction in falls was based on the following: (i) a falling rate of 60% in the control group (as has been observed in older people with foot pain in a previous risk factor study by Menz et al [12]), and (ii) a falling rate of 42% in the intervention group (which equates to a 30% reduction in the number of fallers, recently demonstrated in a similar multifaceted study by Clemson et al [68]). We chose an alpha level of 0.05 and allowed for a drop-out rate of 15%. To allow for unforeseen circumstances we will aim to recruit 300 participants (i.e. 150 per group).

### Statistical analysis

Statistical analysis will be undertaken using SPSS version 14.0 (SPSS Corp, Chicago, Ill, USA) and STATA 8 (Stata Corp, College Station, Tex., USA) statistical software. All analyses will be conducted on an intention-to-treat principle using all randomised participants [69]. Missing data will be replaced with the last score carried forward. Demographic characteristics and baseline data will be summarised by descriptive statistics. Consistent with the recommendations of the Prevention of Falls Network Europe group [43], three falls outcomes will be used as the primary outcomes: the number of fallers, the number of multiple fallers and the falls rate. The number of fallers and multiple fallers (two or more falls) will be compared by calculating relative risks. The number of falls and falls rate per person per year in the two groups will then be compared using negative binomial regression models. This approach takes into account all falls and adjusts for varying duration of follow-up [70,71]. The continuously-scored secondary outcome measures at baseline and the six month follow-up appointments will be compared using analysis of covariance with baseline scores and intervention group entered as independent variables [72,73].

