### Primary outcome measures

All participants will be followed for 12 months following baseline assessment to record the number of falls. Falls, defined as "an unexpected event in which the participant comes to rest on the ground, floor, or lower level" [43] will be monitored using monthly mail-out calendars. When a fall occurs, specific details about fall injuries will be obtained through structured telephone interviews. If falls calendars are not returned at the end of each month, research staff will contact the participants by telephone to obtain the missing data. Consistent with the recommendations of the Prevention of Falls Network Europe group, three falls outcomes will be used as the primary outcomes: the number of fallers, the number of multiple fallers and the falls rate. As a safety measure, the time to first fall will be recorded as a secondary measure to reflect adverse events from the intervention [43].

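### Carrying the last score forward sets every missed six-month secondary outcome to its baseline value, which shrinks true effects and can create false ones; its scope should also be stated to exclude falls

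*Protocol article*

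**What the plan says.** The protocol article's Statistical analysis section gives one general rule for incomplete data: "Missing data will be replaced with the last score carried forward". It comes just after the statement of the analysis set, "All analyses will be conducted on an intention-to-treat principle using all randomised participants", and names no outcome to which it does or does not apply.

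The Secondary outcome measures section sets two assessment times: "All participants will be assessed at baseline and at six months by an assessor blinded to group allocation". The continuous secondary outcomes are to be "compared using analysis of covariance with baseline scores and intervention group entered as independent variables".

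Falls are collected differently. Under Primary outcome measures, "All participants will be followed for 12 months following baseline assessment to record the number of falls", using monthly calendars. For calendars that are not returned, "research staff will contact the participants by telephone to obtain the missing data". The falls rate is analysed by negative binomial regression, of which the plan says: "This approach takes into account all falls and adjusts for varying duration of follow-up". Fallers and multiple fallers are compared by relative risks.

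On expected loss, the Sample size section says "We chose an alpha level of 0.05 and allowed for a drop-out rate of 15" per cent.

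**The concern.** With two visits, a participant who has no six-month score has only one earlier score to carry forward, the baseline. The rule therefore imputes no change, and it does so in both arms whatever the other participants in that arm experienced. This affects foot pain, balance and mobility, which are two of the trial's three aims.

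Two features of the plan make this more than a technicality. First, change in both arms is plausible: foot pain and raised falls risk are entry criteria, and both arms are offered free basic podiatry. Second, drop-out may differ by arm: only the intervention arm has the exercise programme and the request to replace footwear, and the Discussion expects adherence to these to be the harder part. If both arms change and one loses more people, setting the missing scores to baseline pulls the two arm means by different amounts.

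A lesser point concerns falls. Because the rule is unrestricted, read literally it would also apply to fall records. That sits badly with a model chosen because it handles unequal follow-up.

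**Working it through.** **The plan's own figures.** With 60% against 42% fallers, two-sided alpha 0.05 and 80% power (pooled variance under the null):

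n = [1.96 × √(2 × 0.51 × 0.49) + 0.842 × √(0.60 × 0.40 + 0.42 × 0.58)]² / 0.18² = 119.9, so 120 per arm.

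Allowing for 15% loss, 120 / 0.85 = 141.2, so 142, against the 143 stated. The 15% is therefore a real planning figure, and nothing below alters the sample size. With 150 per arm, 15% is 22.5 per arm, or 45 of 300 participants.

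**Bias in the six-month scores.** Notation, in baseline SD units:
- t: true treatment effect
- c: mean change common to both arms
- dC and dI: fractions missing at six months in the control and intervention arms

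Missingness is taken as unrelated to outcome. Randomisation makes baseline independent of arm, so the group coefficient estimates the difference in mean change after imputation:

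estimate = (1 − dI)(c + t) − (1 − dC)c = t(1 − dI) − c(dI − dC)

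The estimate itself does not depend on the baseline correlation; the standard error and type I error do.

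| dC | dI | c | t | Estimate from formula |
|---|---|---|---|---|
| 15% | 15% | any | 0.35 | 0.35 × 0.85 = 0.30 |
| 15% | 15% | any | −0.30 | −0.30 × 0.85 = −0.255 |
| 10% | 20% | −0.4 | 0 | 0.4 × 0.10 = +0.04 |
| 20% | 10% | −0.4 | 0 | −0.4 × 0.10 = −0.04 |
| 5% | 25% | −0.4 | 0 | 0.4 × 0.20 = +0.08 |
| 10% | 20% | −0.4 | −0.30 | −0.24 + 0.04 = −0.20 |

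Simulation (150 per arm, baseline correlation 0.6, 4,000 trials per scenario) agrees: −0.255 to −0.257 for the second row, and 0.042, −0.042, 0.082 and −0.200 for the last four. Analysing only the observed scores recovered the true value each time. In the last scenario power fell from 84% on observed data to 60% under carry-forward.

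**Type I error under carry-forward (no true effect).**
- 10% against 20% drop-out, 0.5 SD common change: about 9%. By arithmetic, the false difference is 0.05 and the SE about 0.088, a ratio of 0.57, so the rejection rate is Φ(−1.96 + 0.57) + Φ(−1.96 − 0.57) = 0.088.
- Same split, 0.8 SD change: about 14%.
- Same split, 0.4 SD change: 7.7%. With 5% against 25%: 15.3%.
- Same split, 0.2 SD change: 5.6%. With 13% against 17% and a 0.5 SD change: 5.9%.
- Equal drop-out with a 0.8 SD change: 5.2%. Unequal drop-out with no common change: 5.1%.

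**Standard error.** The carry-forward analysis reports 0.087 to 0.090, against 0.100 from observed scores. The actual sampling SD of the carry-forward estimate was 0.088 to 0.092, so the reported value is about right for that estimator.

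**Falls.** The size of any effect depends on how the rule would be applied. Assume no true effect, 10% against 20% drop-out spread evenly over the year, a mean of 1.5 falls a year and dispersion 1 (which gives the plan's 60% fallers).
- Count frozen at withdrawal and treated as a full year: rate ratio (1 − 0.20 × 0.5) / (1 − 0.10 × 0.5) = 0.95.
- Count frozen and analysed with the time actually observed: rate ratio 1.00, no bias.
- Last monthly count repeated to month 12: rate ratio 0.99, with more variable counts (variance 4.9 against 3.7 in the arm with 20% drop-out).
- Unobserved months counted as fall-free in the relative risks: 0.96 for fallers and 0.94 for multiple fallers, instead of 1.00.

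**The case against.** **The falls analysis may not be touched at all.** The article uses the word *score* for scales and tests, while falls are a *number* or a *rate*. Falls have their own recovery route by telephone and their own model. A reader might infer that the plan contradicts itself on falls. The documents do not support that: no passage says an incomplete record is treated as a full year, and a frozen count with its true follow-up time is simply the observed analysis. What remains is that the sentence has no stated limit. Telephone recovery would not help for participants who withdraw altogether.

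**The standard errors are not shown to be wrong.** A reader might infer that imputing values makes the reported uncertainty too small. It is smaller than the observed-data standard error, but it matches the sampling variation of the carry-forward estimate, and the test holds near 5% when there is no bias. The harm is an estimate centred in the wrong place.

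**Inflated type I error needs two assumptions that the plan does not give:** unequal drop-out and a sizeable common change. Regression to the mean alone, at a correlation of 0.6, would need entrants about 0.5 / 0.4 = 1.25 SD from the population mean to produce a 0.5 SD shift. Entry requires only one positive foot-pain item, one past fall meets the risk criterion, and several outcomes are not selection variables. This stands, so the inflation is a possibility and not a forecast.

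**Carry-forward is conservative.** With equal drop-out it shrinks the effect, and where both arms improve and the intervention arm loses more people it works against the intervention. But reversing the split reverses the sign, so it cannot be relied on as conservative.

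**Conclusion.** The point holds for the six-month secondary outcomes. It follows from the stated rule and the two-visit schedule, not from anything left to an unseen analysis plan. With equal drop-out unrelated to outcome, the effect shrinks by the fraction missing: about 15% at the plan's own figure, taking 0.35 SD to 0.30 SD. The 15% was set for the trial as a whole, so the loss at six months could be smaller and the shrinkage with it. A false difference arises only if drop-out differs by arm and both arms change; type I error is then about 9% in the 10% against 20%, 0.5 SD case and close to 5% in milder ones. Those splits, shifts and the correlation of 0.6 are assumptions.

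For falls, the finding is limited to unclear scope. It does not establish that the primary outcomes will be biased or that the plan's standard errors are invalid.

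**What to change.** - **Six-month scores:** delete carry-forward. Use baseline-adjusted analysis of covariance under missing at random, or multiple imputation by arm. The second keeps all randomised participants in the analysis, as the plan promises; the first uses only those with a six-month score.
- **Sensitivity:** add one delta-based analysis that shifts the imputed scores away from missing at random.
- **Falls rate:** state that carry-forward does not apply. Analyse observed falls with the log of observed follow-up time as the offset.
- **Fallers and multiple fallers:** an offset does not reach these relative risks. Name a method that allows for incomplete follow-up, for example multiple imputation of faller status for those who withdraw, and do not count unobserved months as fall-free.

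The change is to analysis wording only, with no effect on sample size or conduct, and should be made before the data are analysed. The price is slightly wider intervals and a little more analysis work.

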**Methods:**

Three hundred community-dwelling men and women aged 65 years and over with current foot pain and an increased risk of falling will be randomly allocated to a control or intervention group. The "usual cae" control group will receive routine podiatry (i.e. nail care and callus debridement). The intervention group will receive usual care plus a multifaceted podiatry intervention consisting of: (i) prefabricated insoles customised to accommodate plantar lesions; (ii) footwear advice and assistance with the purchase of new footwear if current footwear is inappropriate; (iii) a home-based exercise program to strengthen foot and ankle muscles; and (iv) a falls prevention education booklet. Primary outcome measures will be the number of fallers, number of multiple fallers and the falls rate recorded by a falls diary over a 12 month period. Secondary outcome measures assessed six months after baseline will include the Medical Outcomes Study Short Form 12 (SF-12), the Manchester Foot Pain and Disability Index, the Falls Efficacy Scale International, and a series of balance and functional tests. Data will be analysed using the intention to treat principle.

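### Three unranked primary falls outcomes with no success rule, while the sample size and its single alpha treat the percentage of fallers as the only primary outcome

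*Protocol article*

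**What the plan says.** The Abstract (Methods) lists the outcomes without an order: "Primary outcome measures will be the number of fallers, number of multiple fallers and the falls rate recorded by a falls diary". The Primary outcome measures and Statistical analysis sections say the same: "three falls outcomes will be used as the primary outcomes: the number of fallers, the number of multiple fallers and the falls rate".

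The Statistical analysis section gives each outcome its own comparison between groups: a relative risk for fallers, a relative risk for multiple fallers (two or more falls), and negative binomial regression for the falls rate.

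The Sample size section works from one outcome. Its 143 participants per group "provides 80% power to detect a 30% reduction in the intervention group in the primary outcome of the percentage of fallers", starting from "a falling rate of 60% in the control group" and 42% in the intervention group. The only error level in the article is there too: "We chose an alpha level of 0.05". It is not divided among outcomes, and no effect size or power is given for multiple fallers or the falls rate.

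**The concern.** The article disagrees with itself on how many primary outcomes there are: three where outcomes and analyses are defined, one where the trial is sized. It also gives no rule for turning three results into one conclusion. Two things follow.

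- **Error rate.** Nothing rules out claiming success on whichever outcome is significant. Under that reading the 0.05 in the sample size calculation is not the error rate of the trial's main claim.
- **Conclusion.** The three outcomes are computed from the same falls but can disagree. If the falls rate is significant and the percentage of fallers is not, the protocol does not say whether the trial is positive, and the emphasis could be chosen after the results are known.

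**Working it through.** **1. The plan's sample size.** Inputs from the Sample size section: p₁ = 0.60, p₂ = 0.42, alpha 0.05, power 80%, drop-out 15%. Sidedness is not stated; two-sided is assumed.

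n = [1.960·√(2·0.51·0.49) + 0.842·√(0.60·0.40 + 0.42·0.58)]² / 0.18² = (1.386 + 0.585)² / 0.0324 ≈ 119.9, so 120 per group.

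With drop-out: 120 / 0.85 = 141.2, so 142 against the stated 143. A one-sided test would give 112. The stated figure is therefore reproduced by one two-sided 0.05 test on fallers, with nothing set aside for two further primary outcomes.

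**2. Numbers analysed.** 143 × 0.85 ≈ 121 per group; 150 × 0.85 ≈ 127 to 128 per group if the full 300 are recruited. Power for fallers at 0.05 is 80% with 121 and 82% with 127.

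**3. Error rate if any one outcome counts.** Three independent tests would give 1 − 0.95³ = 14.3%. These outcomes are correlated, so the figure was simulated.

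- Falls are negative binomial with mean m and dispersion k, so P(no falls) = (1 + k·m)^(−1/k) and m = [(1 − p)^(−k) − 1]/k, where p is the proportion of fallers.
- For k = 1: m = 1/0.40 − 1 = 1.5 when 60% fall, and 1/0.58 − 1 = 0.724 when 42% fall.
- The article gives no dispersion; 0.5 to 2 is assumed.
- Fallers and multiple fallers were compared by two-proportion z tests, and the rate by a negative binomial Wald test with known dispersion.

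No true effect, 60% fallers in both groups, 128 analysed per group, 20,000 trials per setting:

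| Dispersion | Any of three significant, either direction | Any of three significant for benefit | All three significant for benefit |
|---|---|---|---|
| 0.5 | 10.7% | 5.4% | 0.5% |
| 1 | 10.9% | 5.4% | 0.4% |
| 1.5 | 11.2% | 5.5% | 0.4% |
| 2 | 11.2% | 5.5% | 0.3% |

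One two-sided 0.05 test has 5% in either direction and 2.5% for benefit. The any-one rule roughly doubles both; an all-three rule would fall well below them. With 121 per group the results are nearly the same.

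**4. Mixed results under the plan's own effect.** With 60% versus 42% fallers, the chance of a mixed result is P(at least one significant) − P(all three significant). With 128 per group:

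- k = 0.5: 0.979 − 0.766 = 0.214
- k = 1: 0.990 − 0.794 = 0.196
- k = 2: 0.999 − 0.814 = 0.185

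That is about 19–21%. With 121 per group, the number the 80% power rests on, it is about 22–24%.

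**5. What an alpha split would cost.** At 0.05/3 = 0.0167 per outcome, power for fallers falls from 80% to 66% with 121 per group, or from 82% to 69% with 127. Restoring 80% needs 161 per group, and 161/0.85 ≈ 190 after drop-out, 380 in total.

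**The case against.** **A statistical analysis plan may settle this.** A multiplicity rule is often placed there, and that document is not shown. This stands for the detail of any adjustment. It does not remove the disagreement inside the article, which fixes three equal primary outcomes and then sizes the trial on one. The wording of the Sample size section may mean that fallers are the lead outcome, but the sections defining outcomes and analyses do not say so.

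**The inflation is conditional.** This stands. The article gives alpha only for the sample size and sets no test level per outcome, so a reader who says each outcome is tested at 0.05 is inferring it. If all three had to succeed, the error would be far below 5%.

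**The 11% is not the chance of falsely claiming prevention.** This also stands. A reader might take it that way, but it counts differences in either direction, including more falls in the intervention group. The comparable figures are about 5.5% against 2.5%.

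**Power stated for one outcome does not make the others underpowered.** Correct; the article supplies nothing from which to decide. With a 30% relative reduction and an assumed 20–40% of controls falling at least twice, power for multiple fallers is about 25–53% with 128 per group. If instead all falls follow the negative binomial model with 60% versus 42% fallers, it is about 89–94%, and about 97% or more for the rate. At k = 1 that model implies a rate ratio of 0.724/1.5 = 0.48, a 52% cut that the article never posits.

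**Conclusion.** The point holds as an inconsistency within the protocol: three unranked primary outcomes, no success rule, no allocation of alpha, and a sample size built for fallers alone. The consequence is moderate and conditional. If any one significant outcome counts, the family-wise error is about 11% in both directions together, and a false benefit arises in about 5.5% of trials against 2.5% for one test. Under the planned effect, a result the protocol cannot classify would arise in about 22–24% of trials with 121 analysed per group, or about 19–21% if the full 300 are recruited.

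The simulated figures rest on negative binomial falls, an assumed dispersion of 0.5 to 2 and two-sided tests. The inconsistency itself rests on the text alone.

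A reader might also conclude that the falls rate ought to be the primary outcome because it uses every fall. The article does not support that preference: it gives no effect size or power for the rate, so that choice would need a new sample size justification.

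**What to change.** In the Abstract, Primary outcome measures and Statistical analysis sections, name the percentage of fallers over 12 months as the single primary outcome, as the Sample size section already does. Make the falls rate and multiple fallers key secondary outcomes, tested in a stated fixed sequence only after a significant primary result, and reported with estimates and confidence intervals in any case. State that the 80% power applies to the percentage of fallers only.

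The alternative is to keep three primary outcomes with Holm's procedure and restate the power. The 66% (121 per group) or 69% (127 per group) above is a floor for fallers, because Holm is never less powerful than the equal split.

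The first option costs only wording, plus bringing the registry entry into line if it lists three, before unblinding. Sample size, alpha and data collection are unchanged. The downside is that a significant falls rate or multiple-fallers result can no longer carry the primary claim alone. Under the planned effect with 128 per group, P(any significant) − P(fallers significant) is 0.979 − 0.829 = 15% at dispersion 0.5 and 0.999 − 0.831 = 17% at dispersion 2.
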